# STUDY POPULATION

## Population (base)

A) Surgical patients: Patients admitted for elective surgery with planned overnight stay

B) Medical patients: Patients admitted to the medical ward, expected to stay for at least two nights.

As randomization will take place at the department levels (as clusters) rather than at the individual patient level, all patients that are admitted will receive the interventions, but data will be collected only in patients that meet the following inclusion criteria.

## Inclusion criteria

In order to be eligible to participate in data collection for this study, a subject must meet all of the following criteria:

A) (elective surgery patients)

- Adult (18+) patients
- Undergoing elective non-cardiac surgery with planned (postoperative) overnight stay
- Willing and able to provide informed consent
- Able to read and write in Dutch

B) (medical patients)

- Adult (18+) patients on medical departments with expected stay of at least two nights.
- Willing and able to provide informed consent
- Able to read and write in Dutch

## Exclusion criteria

A potential subject who meets any of the following criteria will be excluded from participation in this study:

- Surgical patients: ASA score of 4 or higher
- Surgical patients: PACU admission during first postoperative night
- Planned admission on ICU-ward at any time during admission (for both surgical and medical patients)
- Non-Dutch speaking
- Strict isolation (MRSA, aerogenic)
- Pre-existing delirium or cognitive impairment at inclusion

NB: After starting inclusions, some patients were found to spend the first postoperative night on post-anesthesia care unit (PACU) instead of a WEsleep intervention or control department and after deliberation this was added as a criterium for exclusion.

## Sample size calculation

**Sample size for measuring difference in sleep quality measured by RCSQ between intervention and control group**

Sample sizes of 99 in group SG and 99 in group WG which were obtained by sampling 3 clusters with an average of 33 subjects each in group one and 3 clusters with an average of 33 subjects each in group two, achieve 80% power to detect a difference on the RCSQ between the group means of at least 7.7. We have obtained this difference from Unal et al, using the RCSQ to assess the relation between sleep and delirium prevalence(23). The standard deviation of subjects is 10.27. The intracluster correlation coefficient (ICC) is difficult to predict so we selected a conservative ICC of 0.030. The coefficient of variation of cluster sizes is 0.000. A two-sided t-test was used with a significance level of 0.050. This test used degrees of freedom based on the number of clusters.

In conclusion:

Medical patients:

Intervention (WG): 99

Control group (SG): 99

Surgical patients:

Intervention (WG): 99

Control group (SG): 99

Total: 396 patients.

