## OBJECTIVES

## Primary Objective:

To investigate whether a comprehensive set of low-cost and easily applicable interventions improves sleep quality in hospitalized surgical and medical patients as measured by the subjective Richard Campbell Sleep Questionnaire on the second night of admission for medical patients and first night postoperatively for surgical patients.

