## Primary study parameter

Our primary study parameter is the subjective sleep quality measured by the RCSQ on the second night of admission for medical patients or the first night postoperatively for surgical patients. These were compared between patients admitted into intervention vs. control departments. If data are distributed normally, an unpaired two sided t-test with a significance level of 0.050 will be performed to compare the sleep quality of the intervention group with the control group. If data are not normally distributed, the equivalent non-parametric test will be used.

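### The stated 80% power belongs to a comparison within one specialty (3 v 3 departments), not to the single medical-plus-surgical comparison described as the primary analysis

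*Protocol*

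**What the plan says.** The Sample size calculation (section 4.4, repeated in 10.1.1) takes 3 departments of 33 patients per arm, 99 v 99, and states that these "achieve 80% power to detect a difference on the RCSQ between the group means of at least 7.7". Its other inputs are: "The standard deviation of subjects is 10.27"; "we selected a conservative ICC of 0.030"; no variation in cluster size; "A two-sided t-test was used with a significance level of 0.050"; and "This test used degrees of freedom based on the number of clusters". The conclusion lists 99 intervention and 99 control patients for medical wards and the same again for surgical wards, 396 in all.

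The Randomization section under Treatment of Subjects allocates medical and surgical departments separately, 3 of each per arm.

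The Primary Objective is one question: whether the intervention set "improves sleep quality in hospitalized surgical and medical patients". Section 10.1 (Primary study parameter) defines the outcome night for each specialty and then gives one comparison: "These were compared between patients admitted into intervention vs. control departments". The test is an unpaired two-sided t-test at 0.050, or a non-parametric equivalent. Section 10.1 does not split this comparison by specialty.

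**The concern.** The calculation and the analysis imply different confirmatory structures. Sizing 99 v 99 and then doubling it makes most sense if each specialty was meant to have its own adequately powered test, which would be two primary hypotheses. The objective and section 10.1 state one hypothesis, tested on all 396 patients.

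Two things are at stake. First, the only power figure for the primary outcome is not the power of the test named as primary, so a reader cannot tell from it what difference the trial can detect. Second, the number of primary hypotheses should be fixed before the data are analysed. It also has a practical consequence here, because the protocol makes later roll-out to control departments depend on positive preliminary results.

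**Working it through.** **Inputs.** All are from section 4.4 unless noted: difference 7.7; SD 10.27; ICC 0.030; 33 patients per department; equal cluster sizes; two-sided 0.05; cluster-based degrees of freedom. The 12 departments, 6 per arm, come from the Study Design and Randomization sections.

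**Formulas.** With m patients per department and k departments per arm:

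- design effect DE = 1 + (m − 1) × ICC
- SE = SD × √(2 × DE / (m × k))
- noncentrality = difference / SE
- power from the noncentral t distribution

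**Step 1: reproduce the stated 80% (one specialty, k = 3).**

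- DE = 1 + 32 × 0.03 = 1.96
- SE = 10.27 × √(2 × 1.96 / 99) = 2.044
- noncentrality = 7.7 / 2.044 = 3.77
- df = 3 + 3 − 2 = 4
- power = 80.1%; difference detectable with 80% power = 7.69

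The protocol's figure is reproduced. With patient-level degrees of freedom (196) the same inputs give 96.3%, so the 80% is that of a 3 v 3, cluster-level test within one specialty.

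**Step 2: the comparison in section 10.1, all 12 departments (k = 6).** Assume a common effect, SD and ICC in both specialties, and a test that respects departments and the medical/surgical strata.

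- SE = 10.27 × √(2 × 1.96 / 198) = 1.445
- noncentrality = 7.7 / 1.445 = 5.33
- df = 12 departments − 3 parameters (intercept, arm, stratum) = 9
- power for 7.7 points = 99.7%
- difference detectable with 80% power = 4.55, about 4.6 points

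The choice of degrees of freedom matters little: 8 to 10 df give 99.6% to 99.8% power and a detectable difference of 4.5 to 4.6 points.

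**Step 3: how far the inputs can move before the pooled test falls to 80% power for 7.7 points (9 df).**

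| Held fixed | Limit for 80% power |
| --- | --- |
| ICC 0.03 | SD about 17.4 |
| SD 10.27 | ICC about 0.14 |

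**Step 4: the other reading, two separate primary tests at 0.05.** The departments in the two specialties are distinct, so the tests are treated as independent.

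- chance of at least one false positive when neither effect exists = 1 − 0.95² = 9.75%
- power to succeed in both = 0.801² = 64%

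**The case against.** The strongest defence is that nothing here harms the trial. The power sentence is true as written, because 99 v 99 patients from 3 v 3 departments do give 80%. Sizing each specialty to stand alone and then testing overall is a legitimate conservative choice. The four groups of 99 can be read as recruitment targets that match the separate randomization, and no section plans a confirmatory claim for medical or surgical patients alone. Most of this stands, and it limits how serious the point is. It does not remove the mismatch: section 10.1.1 places the 80% under the primary parameter without saying that it applies to one specialty, and no power is given for the comparison that is planned.

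A reader might infer three stronger things that the protocol does not support:

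- **That the alpha of the primary test is wrong because of the pooling.** One pooled test at 0.05 spends 0.05. The 9.75% needs two separate primary tests, which the objective and section 10.1 do not describe. (A plain patient-level t-test does inflate alpha when departments are correlated, but it does so whether or not the specialties are pooled. That is a separate matter.)
- **That the primary test is underpowered.** On the protocol's own inputs, pooling raises the power.
- **That a 3 v 3 test could never reach significance.** With 20 possible allocations per specialty, a department-level permutation test cannot give a two-sided p below 2/20 = 0.10. However, the non-parametric fallback in section 10.1 replaces a t-test on patients. No department-level permutation test is planned.

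Details such as an interaction test may properly sit in a statistical analysis plan that is not shown. Their absence is not part of this point.

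**Conclusion.** The point holds as an inconsistency between the sample size section and the primary analysis. The 80% for 7.7 points is the power within one specialty (80.1% on 4 df). The comparison described as primary covers both specialties and would have 99.7% power for 7.7 points, or 80% for about 4.6 points, if analysed at department level with strata. The error is in the safe direction for power and has no bearing on alpha under the single-test reading, so it is a correction to make before analysis and not a threat to the trial.

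The pooled figures assume the same effect, SD 10.27 and ICC 0.03 in both specialties, equal cluster sizes, and an analysis that accounts for departments. Without a stratum term, a difference in mean score between medical and surgical patients would lower the power. The 9.75% and 64% apply only if two separate primary tests were intended.

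**What to change.** In sections 4.4, 10.1 and 10.1.1, state one primary test at two-sided 0.05 over all 12 departments, stratified by medical/surgical as in the randomization. It must account for clustering by department, with degrees of freedom based on the number of departments. The cluster adjustment is essential, because the restated power does not hold without it.

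Restate the power for that test. At SD 10.27 and ICC 0.03, 396 patients give 80% power for about 4.6 points. Equivalently, they give 80% power for 7.7 points up to an SD of about 17.4 at ICC 0.03, or up to an ICC of about 0.14 at SD 10.27. State the assumption of a common effect, SD and ICC.

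Report the medical and surgical effects as secondary, with confidence intervals. If two confirmatory tests were in fact intended, say so instead and give the rule for alpha and for declaring success.

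The cost is wording only, with the same 396 patients and 12 departments. The downside of the single test is that neither specialty can support a confirmatory claim of its own.

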**Sample size EEG headband**

We chose sleep efficiency as our primary outcome on the substudy with EEG-headbands. There are no studies using either the Philips or Dreem Headband to compare sleep in two groups. However, polysomnography (PSG) also uses an EEG signal. One study studying sleep parameters using PSG compared groups before either a low or high dose of melatonin, and found a statistical significant difference of 6.24 with a standard error of 1.81 (24). This yields a sample size of 3 in each group, using an unpaired t-test with a power of 80% and significance level of 0.05.

  - Sleep rounds will be implemented. During sleep rounds, patients will be reminded to visit the bathroom before bedtime, and IV bags will be switched to prevent having to change them while the patient sleeps.
  - A sleep menu will be provided to the patients with the patient information brochure. This will include items patients might use to improve their sleep, i.e. a sleep mask, ear plugs and warm blankets and socks.
  - Late night snacking (after 21.00 hours) will be discouraged wherever possible

In the control group care as usual is provided according to the current protocols.

## Randomization

As this is a cluster randomized controlled trial, patients will not be randomized individually. 12 departments will be asked to participate in the trial (6 medical and 6 surgical departments. Medical and surgical departments will be randomized separately, using a standard method of randomization (e.g. randomization.com). This will yield 3 medical en 3 surgical departments in both groups (intervention vs. control). The Intensive Care Unit and the surgical department for Cardiothoracic Surgery will be excluded from randomization. Inclusion of departments will stop when 6 medical and 6 surgical departments are found that are willing to participate.
3 medical and 3 surgical departments will provide care using the WEsleep-protocol from the start of the trial. The other departments will provide standard care during this time.

After the study, we will also implement the interventions at the control departments, as long as the preliminary results are positive.

# INVESTIGATIONAL PRODUCT

**Only applicable for the subjective sleepstudy.**

**Dreem headband**

The Dreem Headband is a compact system for recording brain activity (EEG), movements and breathing frequency

The Dreem can measure: sleep endpoints and quality metrics (determined following the American Academy of Sleep Medicine Definition), hypnograms with associated sleep stages, raw data files, which include EEG channels and breathing rate.

The Dreem 3 headband for research is registered as an FDA Class II Medical Device in the USA.
The Dreem 3 headband is CE marked for electromagnetic compatibility but not considered as a medical device in Europe. It can be used as an investigational device in research studies

Dreem subjects' accounts will be created with pseudonymized names, ages, and gender for the study. Only the main investigator or authorized personnel will have access to the correspondence table that contains both the identity of the subjects and identifiers. Dreem does not have access to any personal data. Upon request, data can be deleted at any time during the study. At the end of the study (or after a few months depending on the agreement), Dreem will delete all the recordings from its server (25).

**Philips Smartsleep Deep Sleep headband**

The Philips Smartsleep Deep Sleep Headband is a wearable system for recording brain acitivity. It measures all sleep metrics.

Measurements are saved offline on the device itself, so only authorized personnel will have access to the results.

It is not a medical device and can be freely bought by people in Europe. It is CE marked (26).

**Withings Sleep Analyzer**

The Withings Sleep analyzer is a system which is placed under a person’s mattress, tracking heart and breathing rates and movement. By monitoring these parameters it is able to differentiate between REM and light and deep non-REM sleep, while also being able to detect sleep apnea disorders.

The Withings Sleep Analyzer can be freely bought by people in Europe and is CE-marked. It has also been used extensively in medical research to track sleep(27).

# NON-INVESTIGATIONAL PRODUCT

Not applicable.

# METHODS

## Study parameters/endpoints

### Main endpoint

Our primary outcome is the subjective sleep quality as measured the Richards-campbells sleep questionnaire.

Subjective sleep quality will be assessed with the Richard Campbell Sleep Questionnaire (RCSQ). The RCSQ measures sleep quality on five questions using a visual analogue scale (VAS), ranging from 0 to 100, with higher scores indicating a better sleep quality. A sixth question was added to assess noise levels (as is quite customary), using a VAS-scale, ranging from 0-100, with a higher score indicating more noise.

### Time of main endpoint

Main endpoint will be measured on the second night of admission for medical patients, first night after surgery for surgical patients.

### Secondary endpoints

- Night-to night changes in subjective sleep quality as measured with the RCSQ.
- Difference in subjective sleep quality between during admission and at home. For this outcome, we will assess the subjective sleep quality at home retrospectively at inclusion.
- Diurnal phase shift of sleep-wake timing: The phase shift of sleep-wake timing will be assessed by comparing midpoint of sleep during admission with midpoint of sleep on a work-free day before admission, both measured with the Consensus Sleep Diary (CSD). For this outcome, we will assess sleep-wake timing at home retrospectively at inclusion.
- Night-to-night changes in sleep-wake timing: The changes in sleep-wake timing (i.e. midpoint of sleep, sleep on- and offset time, sleep duration, sleep latency & inertia and daytime napping), as measured by the CSD.
- Timing of food intake and sleep quality/timing: the association between food intake timing (i.e. first and last meal of the day and whether food was eaten after 21:00h), as measured by asking patients directly for the time of the first and last meal of the day and whether patients ate after 21:00h), and subjective sleep quality and sleep-wake timing (as measured by the Richard Campbell Sleep Questionnaire
- Quality of recovery (for surgical patients) and sleep quality/timing. The association between quality of recovery (in surgical patients), as measured by the Quality-of-Recovery 15 item questionnaire (QoR-15), and subjective sleep quality and sleep-wake timing (as measured by the Richard Campbell Sleep Questionnaire and Consensus Sleep Diary respectively). The QoR-15 will be completed twice by patients.
- 30 day mortality, assessed by checking the medical record retrospectively 30 days after admission.
- 30-day incidence of delirium during admission, as assessed by a physician during admission. Patients will be assessed for delirium at the request of nursing staff or if the score of the Delirium Observation Screening scale is 3 or higher. The Delirium Observation Screening scale ranges from 0 to 39, with higher scores indicating a higher chance of delirium.
- 30-day incidence of surgical site infections (for surgical patients), as assessed by physicians from the department where patient is admitted during hospitalization. If the patient obtained a surgical site infection after discharge, incidence was assessed in the outpatient clinic by a physician from the department where patient was admitted.

Objective sleep substudy:

- Sleep efficiency (objectively measured) during admission. Objective sleep quality will be measured by the Dreem-3 headband, using electro-encephalography (EEG) to differentiate between wakefulness, Rapid-Eye-Movement (REM) sleep and non-REM N1, N2 and N3 sleep. The primary outcome measure will be sleep efficiency (time slept divided by time in bed spent trying to sleep), compared for patients on intervention and control departments.
- Differences in objective sleep measures of sleep-wake timing during admission. Changes in sleep-wake timing (i.e. midpoint of sleep, sleep on- and offset time, sleep duration, sleep latency & inertia) will be compared for patients on intervention and control departments.
- Night-to-night changes in objective sleep measures during admission. The amount of time in each of the different sleep stages and their distribution, as well as total sleep time, will be compared for patients on intervention and control departments.
- Difference between objective and subjective sleep measures during admission. Subjective sleep measured with the RCSQ and CSD.
- Quality of recovery after surgery and objective sleep quality/timing.
- Correlation 30 day mortality and objective sleep quality/timing.
- Correlation 30-day incidence of delirium during admission and objective sleep quality/timing.
- Correlation 30-day incidence of surgical site infections (for surgical patients) and objective sleep quality/timing.

### Time of other study parameters

Secondary endpoints will be measured during admission with a maximum of seven days. If a patient leaves the hospital before these seven days, the measurements will be stopped.

## Randomisation, blinding and treatment allocation

After inclusion in the trial, departments will be randomised by an investigator through online software (e.g. randomization.com) and according to Good Clinical Practice guidelines.

All patients admitted into one of the randomized departments is eligible to participate in the study, provided that the inclusion criteria are met.

**Study procedures**

After obtaining informed consent, patients are provided with the RCSQ and CSD for each day of admission, as well as for a regular night at home (one workday and one work-free day). Filled out questionnaires will be collected daily. Baseline characteristics and relevant data on admission (such as morbidity, length of hospital stay, etc.) will be collected from the patient records. Discharge from the hospital will be the end of the study for each participant.

### Screening and inclusion

Patients will be screened for eligibility by checking patient records of patients admitted into each of the participating departments. Patients that have objected to participating in medical studies will not be approached or screened for eligibility, to comply with AVG requirements.

Patients eligible will be approached at the department they are admitted at and will be included after informed consent has been obtained.

### Randomization

After completion of informed consent procedure, baseline characteristics will be noted. Randomization is on cluster/department level, not individual level.

## Withdrawal of individual subjects

Subjects can object to the use of their anonymized data at any time without any consequences. The investigator can decide to withdraw a subject from the study for urgent medical reasons.

### Specific criteria for withdrawal (if applicable)

Subjects may be removed from the study if any of the following events occur

- Refusal of the subject to continue observations
- Decision by the investigator or healthcare professional that termination is in the subject’s best medical interest

## Replacement of individual subjects after withdrawal

All drop-outs will be replaced

## Follow-up of subjects withdrawn from treatment

Not applicable.

## Premature termination of the study

As there are no risks associated with the study, premature termination and safety reporting is not included in this study protocol.

## In case of postponement of surgery

Not applicable.

# SAFETY REPORTING

As there are no risks associated with the study, premature termination and safety reporting is not included in this study protocol.

# STATISTICAL ANALYSIS

All patients with a total RCSQ score on the primary outcome night (second night of admission for medical patients and first night postoperatively for surgical patients) will be included in the final analysis. The baseline characteristics of all subjects, and per treatment group, will be outlined in a table describing variables such as demographic variables, weight, length, relevant medical history, current medication use, current ASA classification and type of anaesthesia. Continuous data will be presented as mean with standard deviation (SD) or as median with interquartile range (IQR), depending on the distribution of the data. Drop-outs will be replaced. Confounding will be evaluated using a linear regression analysis.

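### The protocol's only analysis set requires a primary-night RCSQ and, as written, also governs 30-day mortality, delirium and SSI; separately, the end-of-measurement wording contradicts the 30-day endpoints.

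*Protocol*

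**What the plan says.** **Analysis set.** The general opening of the protocol's Statistical Analysis section, which precedes the primary and secondary subsections, states that "All patients with a total RCSQ score on the primary outcome night" "will be included in the final analysis". The same paragraph adds "Drop-outs will be replaced". Neither subsection gives another set.

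**Replacement and withdrawal.** The section on replacement after withdrawal says "All drop-outs will be replaced". The withdrawal criteria are refusal to continue and "Decision by the investigator or healthcare professional that termination is in the subject’s best medical interest". Follow-up of withdrawn subjects is marked as not applicable.

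**Clinical outcomes.** The Secondary Objectives frame mortality and delirium for patients admitted to intervention and control departments, with no questionnaire condition. Under Secondary endpoints, mortality is "30 day mortality, assessed by checking the medical record retrospectively 30 days after admission". Delirium is assessed by a physician during admission. SSI is assessed by department physicians, and after discharge in the outpatient clinic. All three are compared between arms by chi-square test.

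**End of measurement.** Time of other study parameters says "Secondary endpoints will be measured during admission with a maximum of seven days". Study procedures says "Discharge from the hospital will be the end of the study for each participant". Study Design follows patients to discharge or for at most seven nights.

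**The concern.** Mortality, delirium and SSI can be ascertained in every consented patient, whether or not a sleep questionnaire was filled in. If the RCSQ condition governs them too, their event rates are conditional on having been well enough to complete a form on one early morning. Delirium and death are themselves reasons for not completing it. Pre-existing delirium is an exclusion criterion, so the patients at issue are new cases, which the delirium endpoint is meant to count.

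Replacement makes the loss hard to see. The target of 33 patients per department is met whatever the number lost, and nothing in the text asks for that number by arm. No blinding is described, and nurses on intervention wards ask patients about their sleep, so completion could plausibly differ between arms.

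The second problem concerns follow-up. Study staff who apply the discharge or seven-day limit literally would stop before the 30-day endpoints are due.

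**Working it through.** **1. The plan's own figure.** The point disputes no stated number. For completeness, the sample-size statement has 3 clusters of 33 per arm in each stratum, difference 7.7, SD 10.27, ICC 0.030, two-sided alpha 0.05 and cluster-based degrees of freedom.
- Design effect = 1 + 32 × 0.03 = 1.96
- SE = 10.27 × √(2 × 1.96 / 99) = 2.044
- Noncentrality = 7.7 / 2.044 = 3.768, with 2 × 3 − 2 = 4 degrees of freedom
- Power = 80.1%, against the stated 80%

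The figure is reproduced, and the fix does not alter it.

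**2. The sections side by side.**

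| Question | One place | Another place |
|---|---|---|
| Who is analysed? | Statistical Analysis: patients with a primary-night RCSQ | Secondary Objectives: for mortality and delirium, patients admitted to the departments |
| When does measurement end? | Study Design, Time of other study parameters, Study procedures: discharge, or seven days or nights | Secondary endpoints and Secondary study parameter(s): mortality checked at day 30; SSI after discharge in the clinic |
| What is the delirium window? | Label: 30 days | Assessment: during admission only |

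**3. Who can be lost.** Consent is taken on the first or second day of admission. The primary night is the second night of admission (medical) or the first postoperative night (surgical). Only a patient incapacitated or dead before giving that score fails the condition. Later events stay in. An SSI before the first postoperative morning is hardly possible, so the mechanism bears mainly on early delirium and early deaths.

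**4. Illustration on assumed rates.** The protocol gives neither event rates nor rates of missing RCSQ, so every input here is an assumption. Let p be true incidence, m the share of delirious patients without a primary-night score, and u the same share among other patients. Then

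rate among completers = p(1 − m) / [p(1 − m) + (1 − p)(1 − u)]

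| p | m | u | Calculation | Rate among completers |
|---|---|---|---|---|
| 10% | 5% | 5% | 0.095 / (0.095 + 0.855) | 10.0% |
| 10% | 10% | 5% | 0.090 / (0.090 + 0.855) | 9.5% |
| 10% | 30% | 5% | 0.070 / (0.070 + 0.855) | 7.6% |
| 10% | 50% | 5% | 0.050 / (0.050 + 0.855) | 5.5% |
| 10% | 70% | 5% | 0.030 / (0.030 + 0.855) | 3.4% |
| 5% | 30% | 5% | 0.035 / (0.035 + 0.9025) | 3.7% |
| 5% | 70% | 5% | 0.015 / (0.015 + 0.9025) | 1.6% |

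Here m refers to all delirium during the admission, not just early delirium. The values of 50% and 70% would need most cases to arise before the primary-night score, so they are probably high.

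**5. Arms that differ in completion.** Take a true incidence of 10% in both arms and 95% completion among other patients. Let 50% of delirious patients complete the score in one arm and 80% in the other:
- 0.050 / (0.050 + 0.855) = 5.5%
- 0.080 / (0.080 + 0.855) = 8.6%

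A gap of about 3 percentage points arises from selection alone.

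**The case against.** The strongest reply is that the sentence says all patients with a score, not only those, and is built around the primary night, so it may be meant for the RCSQ comparison alone. Endpoint-specific sets are also often left to a statistical analysis plan. The first part is a fair reading of intent. But it is the only inclusion rule given, it heads the whole section, it is paired with replacement, and it sits uneasily with the Secondary Objectives. The point rests on what the text fixes, not on what it leaves out.

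Three stronger readings are tempting, and the protocol does not support them.

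- **That everyone without a score is replaced.** The text replaces drop-outs. It does not say that a patient with a missing questionnaire, a transferred patient or one who has died is a drop-out, nor that record data of replaced patients are discarded. The absence of follow-up after withdrawal makes that outcome possible, not certain.
- **That the events of interest are excluded altogether.** Only events in the short window before the primary-night score are at risk. The exclusions for ASA 4 or higher, planned ICU admission, first-night PACU stay and existing delirium or cognitive impairment narrow it further.
- **That deaths and SSI after discharge will be missed.** The endpoint definitions provide for a day-30 record check and for outpatient SSI assessment. The seven-day wording fits the daily questionnaires. Events are lost only if that general wording prevails over the specific definitions.

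**Conclusion.** The concern holds in a limited form. As written, one RCSQ-based set governs the whole statistical section and conflicts with the objectives for mortality and delirium. Selective loss of early delirium and early deaths from the arm comparisons is possible; SSI is hardly affected. Neither size nor direction can be derived from the protocol. The illustrations run from no distortion (equal completion) to a two-thirds understatement (10% shown as 3.4%), and all depend on assumed completion rates.

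The contradiction between the end-of-measurement wording and the 30-day endpoints, and the mismatch in the delirium label, rest on the text alone. The sample size is unaffected. The text should be changed because the correction is cheap and removes an avoidable source of bias in the secondary clinical outcomes.

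**What to change.** 1. In the opening of Statistical Analysis, limit the primary-night condition to the RCSQ analyses.
2. Analyse mortality, delirium and SSI (SSI in surgical patients) in all consented eligible patients, by the allocated arm of their department. Include those without a primary-night score and those replaced, subject to consent for record use.
3. Report the number of missing primary-night scores, with reasons, by arm and by department. Recruitment to 33 primary-night scores per department may continue.
4. In Study Design, Time of other study parameters and Study procedures, exempt the 30-day endpoints from the discharge and seven-day limits.
5. Label the delirium endpoint as in-hospital delirium within 30 days.

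The cost is protocol wording and chart checks for a few extra patients. The test specified for the primary outcome need not change for this point.
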